### ***Primary analysis***

The primary analysis of efficacy will be comparison between Group B and C of the time to first episode of malaria meeting the primary case definition of clinical malaria episode over a period of 6 months of follow up after the last vaccination (ie, from Day 63 to 243). This will be done using survival analysis (e.g. Cox proportional hazard model), adjusting for any stratification factors (age, bednet use). Results will be presented as adjusted hazard ratio with appropriate 95% confidence intervals. Vaccine efficacy will be calculated as 1-HR. Kaplan-Meier methods will be used to visualize the time to first malaria event. The primary analysis will be based on the per-protocol population. An unadjusted analysis will also be carried out on the basis of intention-to-treat.

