## Study site

The study will take place at the Banfora trial site, which is located about 400 km from Ouagadougou, the capital city of Burkina Faso. The URC-B, the research unit is situated within the complex of the Regional hospital. The trial participants will be drawn from Banfora Health demographic system that covers a total population of 30,000 inhabitants. From recent surveys, the bed net coverage was 80%. There is no implementation of Indoor Residual Spray or IPT in infants or children in the area. To date there is no evidence of the decline in malaria incidence that has been recently reported from other parts of sub-Saharan Africa. In Burkina Faso, malaria is endemic. Transmission occurs throughout the year, with a peak during the rainy season (June to October). *P. falciparum* is responsible for more than 90% of all clinical malaria cases. The major vectors are *Anopheles gambiae*, *An. arabiensis* and *An. funestus*. Children under five years and pregnant women are the populations at highest risk. During the five months when transmission reaches a peak, individuals in these age-brackets may suffer multiple malaria episodes, with an annual malaria death toll reaching 15,000 people. In the country's hospitals, malaria is reportedly responsible for 30.7% of all hospitalization with a mortality rate of 23%.

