### ***Screening Visit***

We will provide detailed information about the study for distribution to the parents/guardians. The investigators will endeavour to ensure that all carers fully understand the risks. Any carer who appears to have less than complete understanding will be considered unable to give consent. As with any experimental vaccine the parents/guardians must understand that the vaccines have not yet been shown to prevent infection and this will be stressed during the recruitment stage. They must also understand the very small chance of anaphylactic reactions and thereby the importance of complying with the one-hour observation period after each vaccination. The information sheet covers these points in detail, and each parent/guardians will have the contents of the sheet explained in individual meetings.

If it is determined by the investigator conducting the screening visit that free and informed consent is given by the parent/guardian for their infant/child to participate in the trial, the parent/guardian will be asked to complete the consent form. The parent/guardian will thumbprint the consent form if illiterate.

A literate, impartial witness will be present for screening procedures and countersign the consent form if the parents/carers are illiterate.

Infants/children of parents/guardians who have consented will undergo the full screening procedures. This consists of medical history, physical examination, and blood sampling for screening tests as detailed below (Laboratory Evaluations).

The village of residence of the participant will be documented, along with the GPS coordinates of the homestead.

The investigator will determine whether the infant/child is eligible to participate in the study, using the findings at screening, including the results of the Screening blood tests. Infants/children eligible to participate in the study will fulfil all of the inclusion criteria, and meet none of the exclusion criteria.

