## **Allocation of participants to Study Group and order of enrolment of Study Groups**

Participants are considered enrolled into the study when they have received the first study vaccination.

The study will commence with the Phase 1 lead-in Safety Evaluation. Thirty eligible participants will be identified as above, and allocated to Group A. The participants will be the following ages at enrolment:

- 5 to 8 months: 10 participants
- 9 to 12 months: 10 participants
- 13 to 17 months: 10 participants

For the Phase 2 Trial, 700 eligible participants will be identified as above, and randomised to Group B or C by an independent statistician, who is not one of the investigators. The randomisation will be stratified according to the following age categories, with varying block sizes:

- Participants aged 5-8 months at enrolment
- Participants aged 9-12 months at enrolment
- Participants aged 13-17 months at enrolment

A randomisation list will be generated and sequentially numbered opaque sealed envelopes will be made for the investigators to ensure treatment concealment. The investigators will not be aware of the randomisation result in the envelopes. The randomisation list, which will be password protected, will be kept in confidence until the final primary analysis is being conducted. As described in Section 7, all investigators will be blinded to allocation of participants in the Phase 2b trial to Group B vs Group C, except the staff responsible for the storage and preparation of the study vaccines.

The interim safety data to Day 21 of trial participation of Group A participants will be presented to the DSMB. DSMB review and approval will be required to administer the first vaccination to Group B and C participants.

The interim safety data to Day 63 of trial participation of Group A participants will be presented to the DSMB. DSMB review and approval will be required to administer the second vaccination to Group B and C participants.

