### **Days 57, 58 and 59**

Each subject will be visited at home daily for three days by a field worker for assessment and recording of any solicited and unsolicited AEs . If necessary the volunteer will continue to be seen regularly until the AEs have resolved or stabilised.

At the Day 57 visit, the fieldworker will document the bednet use and residual spraying.

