### **Days 123, 153, 183, 213**

Each subject will be visited at home every 30 days by a field worker for assessment and recording of the subject health status. All the children found febrile/history of fever within the last 24 hours will be referred to the research centre where a blood smear will be obtained for malaria diagnosis. Any serious adverse event not detected will be documented. If necessary the volunteer will continue to be seen regularly until the AEs have resolved or stabilised.

At Study days 213 visit, the fieldworker will document the bednet use and residual spraying.

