#### ***-Efficacy against secondary case definitions of clinical malaria episode***

- Time to first episode of malaria meeting the secondary case definitions of clinical malaria episode over a period of 6, 12, and 24\* months of follow-up after the last vaccination.
- Proportion of participants with an episode of malaria meeting the secondary case definitions of clinical malaria, within a period of 6, 12 and 24\* months of follow up after the last vaccination

Time to first or only episode of clinical malaria meeting secondary endpoint definitions will be analysed as above.

Variation in efficacy over time will be examined using Schoenfeld Residuals, and time dependent covariate analysis in Cox Regression. If significant variation in efficacy over time is identified then efficacy will be presented as a summary figure over the full length of follow up, but also as a varying figure over time.

The proportion of children with asymptomatic parasitaemia at the cross-sectional surveys will be presented, and vaccine efficacy evaluated using logistic regression.

Multiple episodes of malaria will be examined using Poisson or negative binomial models on the ATP cohort (negative binomial if the data is over-dispersed) and adjusted incidence rate ratios calculated, adjusted by stratification factors. An unadjusted ITT analysis will also be conducted.

\* Depending on the outcome of the efficacy analysis of the 12 month data, this may be extended to 24 months following completion of vaccination

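### Primary model lists bednet use as a stratification factor, but randomisation is stratified by age alone, bednet use is first recorded on Day 57, and the ITT analyses omit age

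*Protocol*

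**What the plan says.** **Primary model.** Protocol section 9, Primary analysis, compares time to first episode between Groups B and C from Day 63 to Day 243 by survival analysis, with Cox regression as the example, "adjusting for any stratification factors (age, bednet use". The population is per-protocol. The same section adds: "An unadjusted analysis will also be carried out on the basis of intention-to-treat".

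**Multiple episodes.** In the secondary efficacy analyses, the Poisson or negative binomial models on the according-to-protocol cohort are adjusted by stratification factors, followed by: "An unadjusted ITT analysis will also be conducted".

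**Randomisation.** Section 8, on allocation to study groups, states: "The randomisation will be stratified according to the following age categories, with varying block sizes". The categories are 5–8, 9–12 and 13–17 months. No other factor is listed.

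**Bednet records.** The Screening Visit section says of the screening procedures: "This consists of medical history, physical examination, and blood sampling for screening tests". It also records village and GPS coordinates, but no bednet item. The Day 0 section and Table 1 have none either. The first record is in the section for Days 57, 58 and 59: "At the Day 57 visit, the fieldworker will document the bednet use and residual spraying". The second is at a later home visit: "At Study days 213 visit, the fieldworker will document the bednet use and residual spraying". Further records follow on Days 393 and 753.

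**The concern.** Three things do not fit together.

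1. The parenthesis calls bednet use a stratification factor, and the allocation section shows it is not one. Taken literally, the clause allows two primary models: age alone (the actual strata) or age plus bednet use (the list in brackets).
2. On the second reading, the covariate has no pre-randomisation value, and the clause does not say which record is meant. The Day 57 value is post-randomisation. The Day 213 value is recorded 30 days before the primary window closes, after many first episodes may already have occurred, and an episode could itself change net use.
3. The ITT models leave out the age bands that the randomisation used. The per-protocol and ITT results then differ in population and in model at once, so a gap between them cannot be put down to protocol adherence.

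At stake are a single, unambiguous primary estimate and a clean comparison of that per-protocol estimate with the ITT result.

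**Working it through.** **Step 1. Timing.**

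| Event | Study day |
|---|---|
| Randomisation and first vaccination | by Day 0 |
| Second vaccination | 56 |
| First bednet record | 57 |
| Endpoint collection starts | 63 |
| Second bednet record | 213 |
| Primary window ends | 243 |

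The Day 57 record falls one day after the second vaccination and 63 − 57 = 6 days before endpoint counting. The Day 213 record falls 213 − 63 = 150 days into a 180-day window.

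**Step 2. Reproduce the stated power.** Inputs from the Sample size section: 700 children allocated 1:1, 50% versus 38% with malaria, hazard ratio (HR) 0.7. Alpha is not given with the power statement; two-sided 0.05 is assumed from the 95% confidence intervals.

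Power = Φ(√(d/4) × |ln HR| − 1.96), where d is the number of events.

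- Base case: d = 350 × (0.50 + 0.38) = 308. √77 × 0.3567 = 3.130, and Φ(1.170) = 87.9%, against 88% stated.
- With 20% loss: d = 0.8 × 308 = 246.4, giving 79.9%, against 80% stated.
- For 40% versus 30%: d = 350 × 0.70 = 245, giving 79.7%, against 79% stated (Freedman's formula gives 78.9%).

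The power figures stand and do not depend on the covariate list.

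**Step 3. What age adjustment would do to ITT power.** The Protocol gives no age gradient in malaria hazard, so a factor g of 1.25, 1.5 or 2 per band is assumed, with three equal bands. The control hazards are λ, λg and λg², with λ set so that the mean Group C risk is 50%. The within-band HR θ is set so that the mean Group B risk is 1 − 0.5^0.7 = 38.4%, the whole-arm proportion behind the Protocol's 38%. Events: 350 × (0.50 + 0.384) = 309.5. The unadjusted HR is the large-sample Cox estimate with age omitted. Both powers use the Step 2 formula.

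| g per band | Within-band HR θ | Unadjusted HR | Unadjusted power | Age-adjusted power |
|---|---|---|---|---|
| 1.25 | 0.698 | 0.700 | 88.1% | 88.6% |
| 1.5 | 0.692 | 0.699 | 88.3% | 90% |
| 2 | 0.676 | 0.698 | 88.6% | 93.0% |

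**Step 4. Does the choice of covariates move the estimate?** A simulation used 700 children, a true HR of 0.7, 50% control incidence, 80% net coverage (from the Study site section), an assumed bednet HR of 1.0, 0.7 or 0.5, an assumed age HR of 1.0 or 1.3 per band, and 400 replicates per scenario. Across the unadjusted, age-adjusted and age-plus-bednet models, the estimated HR ranged from 0.695 to 0.705 and power from 87.5% to 90.2%. Net use was drawn independently of allocation, so this says nothing about bias if allocation did influence net use. It shows only that the choice matters little numerically when it did not.

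**The case against.** The strongest defence is that this is a label error with little consequence.

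- **Timing and blinding.** The Day 57 record precedes endpoint counting on Day 63. Families and the staff assessing endpoints are blinded, and parents are told not to expect protection and to keep using nets. Bias would need allocation to have changed net use by Day 57, and nothing in the Protocol shows that. This stands. A reader might infer that adjusting for the Day 57 value forfeits the protection of randomisation; the documents do not support that.
- **Relevance.** First vaccinations are planned for March–April and second vaccinations for May, ahead of the June–October season. A Day 57 value is nearer the exposure period than a Day 0 value. This also stands, and it is a real cost of moving the question.
- **Power.** A reader might infer that the unadjusted ITT analysis falls below its planned power. If 0.70 is taken as the within-band HR, the same gradients give unadjusted HRs of 0.702, 0.707 and 0.720 and power of 87.5%, 86.3% and 82.7%. But the Sample size section fixes whole-arm proportions. Holding those, Step 3 shows no loss. The shift in HR is the difference between a conditional and a marginal hazard ratio, not bias.
- **Coverage.** Applying 80% survey coverage to the trial gives about 0.2 × 700 = 140 non-users. That is the size of a covariate level and measures no bias.
- **SAP.** A full SAP is promised before unblinding, and an unadjusted supportive analysis is an ordinary choice. True, but the Protocol itself names the covariates and names one wrongly. Choosing a bednet record in the SAP would not create a pre-randomisation value, which has to be collected at the time.

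**Conclusion.** The point holds as an error in how the primary model is specified. Bednet use is listed as a stratification factor when age band is the only one. It has no pre-randomisation record. The ITT models for both first and multiple episodes omit age, so the per-protocol and ITT results differ in two respects at once.

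The numerical effect is modest. The stated 88% power is reproduced. Age adjustment is an efficiency gain for ITT, from about 88% to about 89–93%. That rests on assumed gradients of 1.25 to 2 per band (the last meaning a fourfold hazard difference between the youngest and oldest bands), equal band sizes, and two-sided alpha of 0.05. No bias from the Day 57 record is demonstrated. The Day 213 record is the less defensible choice because it lies inside the endpoint window, and the current wording does not exclude it.

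**What to change.** 1. In Primary analysis and in the multiple-episode paragraph, name the three randomisation age bands as the only stratification factor.
2. Stratify or adjust both the per-protocol and the ITT models by those bands, for time to first episode and for multiple episodes. Keep the unadjusted ITT as a supportive analysis.
3. Define bednet use separately as a covariate. Either add the question at Screening or Day 0 and use that value, or use the Day 57 record in a sensitivity analysis only.
4. State that bednet records from Day 213 onwards are not covariates in the 6-month primary model.

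The cost is one added CRF question at an existing visit plus changes to the analysis wording. A Day 0 value would be recorded further from the transmission season; keeping the Day 57 record for sensitivity analysis limits that loss. The added question has to be settled before enrolment, because a baseline value cannot be recovered reliably later.

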| Review contraindications to vaccination                                                                 |             | X                                |            |       |        | X                     |             |       |     |                     |      |                          |      |                                                       |      |
| Recording of concomitant medication                                                                     | X           | X                                | X          | X     | X      | X                     | X           | X     | X   | X                   | X    | X                        | X    | X                                                     | X    |
| Recording of solicited and unsolicited adverse events                                                   |             | X                                | X          | X     | X      | X                     | X           | X     | X   |                     |      |                          |      |                                                       |      |
| Recording of SAEs                                                                                       |             | X                                | X          | X     | X      | X                     | X           | X     | X   | X                   | X    | X                        | X    | X                                                     | X    |
| Blood Film for P. falciparum                                                                     | X           |                                  |            | X     |        | X                     |             | X     |     |                     | X    |                          | X    |                                                       | X*   |
| Blood Film for P. falciparum if axillary temp ≥37.5 and/or history of fever within last 24 hours |             | X                                | X          | X     | X      | X                     | X           |       | X   | X                   |      | X                        |      | X                                                     |      |

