### **Day 0 (Vaccination)**

This visit will occur not more than 30 days following the screening visit. If more than 30 days have elapsed since screening, then a repeat Screening Visit will be conducted. Medical

history, temperature monitoring +/- physical examination will be performed. Blood sampling will be performed as detailed below (Laboratory Evaluations).

Ongoing eligibility for participation will be confirmed according to the inclusion and exclusion criteria, prior to blood sampling and vaccination. Blood sampling will be performed as detailed below (Laboratory Evaluations).

Infants are considered enrolled into the study when they receive the first study vaccination. The vaccine will be administered as detailed in Section 7 and according to local SOPs.

Following vaccination, the vaccination site will be covered with a dressing which will be removed after 30 minutes. The volunteer will be monitored for one hour (or longer if necessary) after vaccination.

The CRF will be updated.

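### The screening malaria film, taken from every child, could enter the primary Cox and multiple-episode models as a pre-specified covariate: a free but probably small gain in power

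*Protocol*

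**What the plan says.** Tables 1 and 3 both carry a row "Blood Film for P. falciparum" with a mark in the screening column that does not depend on fever, for Groups A, B and C alike. Parasitaemia does not appear among the exclusion criteria in Section 6, so children with a positive film can be enrolled.

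In Section 9, Primary analysis, the Cox model on the per-protocol population is specified as "adjusting for any stratification factors (age, bednet use"). The intention-to-treat counterpart carries no covariates: "An unadjusted analysis will also be carried out on the basis of intention-to-treat". For multiple episodes, Section 9 asks for "adjusted incidence rate ratios calculated, adjusted by stratification factors". For asymptomatic parasitaemia at the cross-sectional surveys it says only "vaccine efficacy evaluated using logistic regression" and lists no covariates.

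On allocation, Section 8 states "The randomisation will be stratified according to the following age categories, with varying block sizes"; age is the only factor listed there. On timing, the Day 0 section states "This visit will occur not more than 30 days following the screening visit", and Study site states "Transmission occurs throughout the year, with a peak during the rainy season (June to October").

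**The concern.** A child's infection status before vaccination is a plausible predictor of later clinical malaria. Section 2.3 itself says that P. falciparum infection may impair T cell responses and may raise the risk of further episodes. The legend of supplementary figure S1 refers to participants with a positive smear at day 0, so such children did occur, though it gives no number.

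The protocol does not leave the primary model's covariates open. It names two and omits this one, although it is measured before allocation in every child and costs nothing more to use. In a Cox model with many events, leaving out a strong predictor gives a marginal hazard ratio closer to 1 than the conditional one, with less power. The plan's own power has little slack in its less favourable cases: 80% with 20% drop-out, and 79% if control incidence is 40%.

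**Working it through.** **1. The plan's own power.** Inputs from Section 5, Sample size: 350 per arm, control risk 50%, Group B risk 38%, hazard ratio 0.7. Alpha is not stated; two-sided 5% is assumed from the 95% confidence intervals. With d events and 1:1 allocation, Schoenfeld's formula gives power = Φ(√(d/4) × |ln HR| − 1.96), where |ln 0.7| = 0.3567.

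- Base case: d = 350 × (0.50 + 0.38) = 308. √77 × 0.3567 − 1.96 = 1.17, power 87.9% (stated 88%).
- 20% drop-out: d = 280 × 0.88 = 246.4. √61.6 × 0.3567 − 1.96 = 0.84, power 79.9% (stated 80%).
- 40% v 30%: d = 350 × 0.70 = 245. √61.25 × 0.3567 − 1.96 = 0.83, power 79.7% (stated 79%).

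The stated power reproduces.

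**2. Gain from adding the film.** Assumptions, none of them given in the documents: 5–30% of children film-positive, and a hazard ratio of 1.5, 2 or 3 for a positive film. Simulation: 4,000 trials per setting, 350 per arm, exponential times over the six-month window, baseline hazard set so that overall control risk is 50%, and a vaccine hazard ratio of 0.7 conditional on the film. Power without → with the film in the Cox model:

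| Film-positive | HR 1.5 | HR 2 | HR 3 |
|---|---|---|---|
| 5% | 87.3 → 87.4% | 87.3 → 88.0% | 86.4 → 88.0% |
| 10% | 87.2 → 87.3% | 87.0 → 88.0% | 85.1 → 87.4% |
| 20% | 87.6 → 88.3% | 86.5 → 88.1% | 82.2 → 87.8% |
| 30% | 87.1 → 87.9% | 85.6 → 87.9% | 82.3 → 88.0% |

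The gain is about 0 to 2.4 points for hazard ratios of 1.5 to 2. At a hazard ratio of 3 it is about 2 points with 5–10% positive and a little under 6 points with 20–30% positive. Adjustment lowered power in none of the 12 settings.

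**3. Same question with the plan's marginal target held fixed.** Section 5 plans on overall risks of 50% and 38%, which correspond to a marginal hazard ratio of 0.7 (1 − 0.5^0.7 = 38.4%). If the simulation fixes those overall risks instead, unadjusted power stays at 87–88% and the unadjusted hazard ratio averages about 0.70. Adjustment still adds about 4.5 points with 20% positive at a hazard ratio of 3. For hazard ratios of 1.5 to 2 the gain stays within the 0 to 2.4 point range. Steps 2 and 3 together give the 4 to 6 point range for the strong-predictor case.

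**4. Age of the film.** Screening runs from Day −30 to Day −1 and endpoint collection starts at Day 63. The film is therefore 63 + 1 = 64 to 63 + 30 = 93 days old when the efficacy window opens. Groups B and C are planned to be first vaccinated in March–April 2013, before the seasonal peak. Both facts may weaken its predictive value.

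**5. Which film.** Both tables schedule the screening film. Table 3 also marks a routine film at Day 0; Table 1 marks only a fever-triggered one there. The routine films at Days 7, 56 and 63 fall after the first randomised vaccination and cannot serve as baseline covariates.

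**The case against.** The strongest reply is that nothing here is wrong. The analysis is valid without the film, the stated power holds, and a detailed analysis plan is promised before unblinding. Covariates are commonly settled there, and the protocol's wording does not rule the film out. The size of any gain rests on assumed figures, and the film is old and pre-seasonal.

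Most of this stands and limits the point to an efficiency gain. It does not remove it. For the primary and multiple-episode models the protocol does state what is adjusted for. It already goes beyond the true design factor: randomisation is stratified by age alone, and bednet use is first scheduled to be recorded at Day 57, after randomisation. That is a separate matter, but it shows that the covariate set was chosen rather than left open.

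Three stronger readings are tempting, and the documents support none of them.

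- A reader might infer that the trial is underpowered for want of this covariate. It is not: with the planned marginal risks, unadjusted power is 87–88%. The lower unadjusted figures in the table arise because there the 0.7 is set conditional on the film, which gives the unadjusted comparison a weaker marginal effect than the plan assumes.
- A reader might infer that efficacy will be understated. With 20% positive at a hazard ratio of 3, a simulated unadjusted hazard ratio of 0.716 against 0.698 adjusted (28% against 30% efficacy) can look like bias. It is the difference between a marginal and a conditional hazard ratio, two different estimands. The plan's sample size is written for the marginal one.
- A reader might count the survey logistic models as a fault too. The protocol names no covariates there, so nothing is fixed badly. The survey endpoint also requires absence of fever and of recent fever history, so the film is not strictly its baseline value.

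**Conclusion.** The point holds as an improvement, not as an error. A pre-vaccination measurement scheduled for every child is left out of the two efficacy models whose adjustment the protocol describes. Using it would be expected to add about 0 to 2.4 points of power if it is a weak to moderate predictor. About 4 to 6 points would need infection to triple the hazard in 20–30% of children, which nothing in the documents establishes. If positive films are rare, or if a film 64 to 93 days old says little about the window from Day 63 to Day 243, the gain is close to nil. These figures rest on assumed prevalence and prognostic strength, a two-sided 5% test and exponential event times.

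**What to change.** Before unblinding, specify the screening film result (positive/negative) as a covariate alongside the age stratum in the primary Cox model and the multiple-episode model. Name the screening film explicitly, because both tables schedule it. Keep the unadjusted estimates as supportive, and state in the report that the adjusted hazard ratio is conditional on baseline infection. Reconcile Tables 1 and 3 on whether a routine film is taken at Day 0. For the survey logistic models, the same covariate is only a suggestion for the analysis plan.

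The cost is one pre-specified line and one table correction, with no new visit, sample or child. The one consequence to accept is the change to a conditional estimand, which the supportive unadjusted analysis covers.
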